**Protocol #: 16-0510**

**Project Title:** Values and Hypertension Study

**Principal Investigator:** [name]

**Version Date:** 12-05-20

**Hypotheses and Specific Aims:** The objective of the study is to reduce the effects of stereotype threat on the adherence of African American patients with hypertension. We hypothesize that stereotype threat impairs communication between minority patients and their providers resulting in decreased patient engagement and lower rates of adherence with antihypertensive medication. We propose an innovative approach using values affirmation to overcome the stereotype threat to increase patient activation, improve adherence and thereby reduce disparities in hypertension outcomes. Our proposal is based upon our pilot study demonstrating a brief values affirmation exercise done immediately before a clinic visit resulted in improved communication between African American patients and providers during the visit and suggested improved medication adherence 6-months after the visit. We propose to advance our prior work and fill gaps in the evidence by conducting a randomized controlled trial comparing a values affirmation exercise to a control exercise among 1,130 patients with hypertension from three health systems. The primary outcome is 6-month adherence to antihypertensive therapies with the secondary outcomes of blood pressure, time under blood pressure control, and treatment intensification. We will also explore possible mechanisms of the intervention effect and formally examine the potential for widespread dissemination.

The specific aims are to:

**Aim 1.** Compare the effects of the values-affirmation exercise to a control condition on antihypertensive medication adherence in African American patients with uncontrolled hypertension across three clinical settings.

**H1:** Those performing the values-affirmation exercise will have increased antihypertensive medication adherence over the ensuing 6-months compared to the control condition

**H2:** The effect of values affirmation will be partially moderated by patient factors (prior experience with discrimination), and provider factors (implicit racial bias, past disparities training, self-efficacy for caring for minority patients), and mediated by the theory-driven factors of patient activation, attitudes, perceived social norms, perceived behavioral control and anticipated emotion regarding management of blood pressure.

**Aim 2.** Compare the effects of the values-affirmation exercise in African American patients and white patients with uncontrolled hypertension and similar socioeconomic characteristics.

**H3:** Values-affirmation will improve antihypertensive medication adherence to a greater degree in African American patients than whites, consistent with the hypothesis that values affirmation is targeting stereotype threat related to race.

**Aim 3.** Evaluate the intervention for widespread dissemination using the RE-AIM (reach, effectiveness, adoption, implementation and maintenance) framework.

**H4:** The intervention will be suitable for more widespread dissemination within primary care.

## II. Background and Significance:

### 1.0 Significance

### 1.1 African Americans have a higher prevalence of uncontrolled hypertension than white Americans leading to disparities in cardiovascular outcomes.

One in 3 US adults has hypertension and African Americans are disproportionately affected; almost 40% of non-Hispanic blacks have hypertension. Although the rates of uncontrolled hypertension have been decreasing in all groups, African Americans continue to have higher rates of uncontrolled hypertension compared to white Americans. Uncontrolled hypertension disproportionately affects outcomes in African Americans compared to whites. A 10-mm Hg difference in systolic blood pressure (SBP) is associated with an 8% increase in stroke risk for whites, but a 24% increase in risk for African Americans. Lower adherence to treatment recommendations may contribute to higher rates of uncontrolled hypertension among African Americans. Therefore, interventions to improve adherence have the potential to reduce racial disparities in hypertension outcomes.

### 1.2 The Institute of Medicine, World Health Organization and others have identified poor adherence to medications as the most significant, modifiable contributor to uncontrolled hypertension.

The prevalence of poor adherence to antihypertensive medications ranges from 43% to 78%, with approximately 50% of hypertensive patients discontinuing the use of their medications after 1 year. Poor adherence to antihypertensive medications is associated with poor outcomes and improving adherence reduces BP. Adherence rates are lower in African Americans than whites with hypertension, and non-adherence has been shown to contribute to racial differences in hypertension control. Therefore, interventions to improve adherence have the potential to reduce racial disparities in hypertension outcomes.

### 1.3 Stereotype threat may contribute to low adherence.

Stereotype threat occurs when cues in the environment (such as visiting a doctor's office) trigger the threat of confirming, as self-characteristic, a negative stereotype about one's group. Although any individual may experience stereotype threat, African Americans are at greater risk due to widespread racism and past experiences of discrimination. In the clinical setting, African American patients report stereotype threat related to being viewed as unintelligent, "second class citizens", and unworthy of good care.

Stereotype threat triggers psychological and physiological responses including reduced memory capacity, impaired communication, disengagement and reduced motivation. Stereotype threat may thus contribute to racial disparities in non-adherence to treatment by hindering a patient's ability to process information and actively engage in a discussion about their health during a clinical encounter. Based on this poor clinical interaction, the patient may feel less activated to adhere to treatment recommendations. Therefore, interventions targeting stereotype threat have the potential to reduce disparities among populations that experience widespread discrimination. (Figure 1)

### 1.4 Values affirmation interventions reduce stereotype threat and decrease racial disparities in academic performance.

Values affirmation exercises typically ask participants to write a few sentences about their core values. By focusing on values that are important to them, such as friends and family, religion, or art, values affirmation bolsters the person's self-concept by helping them view themselves as adequate, effective, and able to control important outcomes in spite of a possible threat. Values affirmation interventions have been associated with reduced stress and improved academic performance among stigmatized group members. Specifically, Cohen et al (consultant on this proposal) demonstrated participation in an affirmation exercise at the beginning of an academic term reduced racial achievement gaps among African American children by 40%; these effects were sustained two years later. Miyake and colleagues performed a similar study

[figure not shown]

with college students in an introductory physics course, and found that values affirmation significantly diminished the gender gap in grades over a semester. Walton and Cohen used a related intervention among white and African American college freshman and found the racial gap in grade point average closed by approximately half over three years of follow-up. Importantly, African American students in the intervention group reported better overall health and fewer doctor visits up to 3 years after the intervention. Overall, this literature provides strong support that a brief psychological intervention targeting stereotype threat can have large and sustained effects on racial disparities in outcomes.

**1.5 We hypothesize that a values affirmation intervention will reduce racial disparities in adherence.** Based on the evidence supporting the effectiveness of values affirmation in educational settings, we hypothesize that values affirmation can similarly reduce racial disparities in adherence and subsequent health outcomes. Our proposed project grows from a theoretical model suggesting patient adherence to prescribed therapies and subsequent control of hypertension are dependent upon the quality of the patient-provider interaction and resultant patient activation. (Figure 1)

The patient-provider interaction provides an opportunity for information exchange and the quality of the interaction is associated with patient adherence to prescribed therapies. Our group and others have shown that healthcare providers have implicit racial biases that are associated with poor communication. From the patient perspective, these subtle experiences of bias can result in stereotype threat. Such threat increases anxiety, reduces memory, and may impair the patient's communication and ability to absorb information. For example, an African American patient, who is experiencing stereotype threat, may alter their behavior during a clinical interaction by failing to ask questions or engage in a discussion about their blood pressure, or to anticipate barriers to adherence. The resulting poor interaction may increase stereotype threat and, a self-fulfilling feedback loop, reinforce a provider's perception that the patient is disengaged or unintelligent. Due to this negative, self-perpetuating cycle, stereotype threat may alter both patient and provider perceptions and decision-making, and, over time, contribute to health disparities. Importantly, stereotype threat may occur in the absence of actual bias in that specific situation, since reminders of prior experiences of bias can trigger it. Therefore, intervening on stereotype threat might lead to independent effects beyond interventions directed at providers. (Figure 1)

The patient-provider interaction is only the first step in care of a chronic condition. Most of the real work of hypertension control takes place away from the clinic, in the form of self-care. Patients must make appointments, maintain prescriptions, take medications, and follow dietary and exercise plans. Because the patient-provider interaction initiates patient activation with self-care, an interaction distorted by stereotype threat can cause significant and lasting damage to hypertension care. Increased patient activation is associated with increased adherence. We hypothesize that values affirmation, by enhancing the patients' resources for overcoming stereotype threat, improves patient-provider communication leading to improved patient activation and adherence.

**1.6 Targeting provider racial bias is another potential approach to improving patient-provider interactions; however, intervening upon provider racial bias presents numerous challenges.** Provider racial bias and discrimination contributes to poor communication and disparities. We will measure racial bias as a potential moderator of the intervention's effect; however, directly intervening upon these processes goes beyond the scope of this study in several ways. First, the provider processes that contribute to disparities are complex and likely implicit, or out of providers' conscious control, making them very difficult to intervene upon. Although implicit attitudes have been malleable in experimental settings, comparable methods have not been tested in a clinical setting with relevant outcomes. Second, our group and others have demonstrated that implicit racial bias is common among health care providers. Changing attitudes throughout a healthcare system is an ambitious and perhaps unrealistic goal. Third, interventions targeting bias among providers have typically relied upon diversity or cultural competency training; however, the evidence for the effectiveness of cultural competency training on reducing health disparities has been modest. Cultural training standards often include approaches like stereotype suppression that have not been effective for reducing implicit bias. Despite these limitations, we recognize

the potential benefit of cultural competency training programs and we will assess exposure to past training as a potential moderator of the intervention's effect. Finally, any program that requires substantial time commitments from clinicians has a lower likelihood of being widely adopted or implemented. Therefore, we have chosen to focus on a low-resource intervention to assist patients that could be easily integrated into routine clinical practice and has been shown to be effective in field settings including health care.

#### 1.7 Our pilot work suggests values affirmation improves patient engagement and

**adherence.** This investigative team tested the theoretical model in a pilot study that informed the current proposal. At a single clinical site, 151 African Americans patients with hypertension were randomized to perform either a values-affirmation exercise or a control exercise immediately before a scheduled visit with their primary care physicians (all who were white). In a subset of 99 patients, patient-provider communication was assessed by analyzing audio recordings with the Roter Interaction Analysis System. This system codes each speech segment based on its content and delivery, and provides global ratings of the emotional tone of the participants' speech. Finally, pharmacy records were used to compare adherence in the six-month period before the index visit with the six-months after the index visit. The intervention had benefit in two areas:

- Patients in the affirmation intervention exchanged more information about their medical conditions, and their encounters were characterized as more engaged than patients in the control condition.

|                                                           | Intervention | Control    | P    |
|-----------------------------------------------------------|--------------|------------|------|
| Mean number of utterances about medical condition (SE)    | 66.3 (6.8)   | 48.1 (5.9) | 0.03 |
| Mean rating of patients' emotional tone (SE)       |              |            |      |
| Interested, friendly, responsive, interactive, respectful | 5.1 (0.1)    | 4.8 (0.1)  | 0.02 |
| Depressed and distressed                                  | 1.1 (0.2)    | 1.5 (0.1)  | 0.03 |

- Patients in the affirmation intervention showed improved medication adherence (mean percentage of days covered for a composite of antihypertensive medications) in the 6 months after the index visit, whereas control patients did not (unpublished data, manuscript under review).

|                                  | Before Visit | After Visit | P*   |
|----------------------------------|--------------|-------------|------|
| Intervention mean adherence (SD) | 74% (22)     | 83% (14)    | 0.01 |
| Control mean adherence (SD)      | 83% (18)     | 81% (17)    | 0.45 |

\* for the time x adherence interaction term, p = 0.02

Mediational analysis suggested that *improved adherence was mediated by an increase in information exchange during the visit*. These findings support the concept that values affirmation in the clinical setting can increase patient engagement in health care. (Figure 1)

#### 1.7 While we have enthusiasm for the results of the pilot work, knowledge gaps remain that will be addressed in the proposed study.

The pilot study was carried out at a single site and only among African Americans. The possibility exists that the threat being blunted by the values affirmation exercise is the more general threat of illness rather than stereotype threat related to race, and thus the exercise could benefit all patients (whites included) and not just African Americans. Since stereotype threat is not readily measured directly, it must be inferred from differential effects of manipulation between groups. Further, possible patient (past discrimination) and provider factors (racial attitudes) that may moderate the effects have not been examined. Finally, the feasibility of wide dissemination of the intervention has not been formally evaluated. Thus, it is premature to consider the values affirmation a general means to address the contribution of stereotype threat to health disparities. To address the limitations of the pilot study, we propose to expand the investigation to 9 clinical sites across multiple systems, compare the effects in African Americans and white Americans, explore possible moderators (i.e. past discrimination, provider racial attitudes) and mediators (i.e. patient activation), and formally evaluate dissemination.

**2.0 Innovation.** Our proposal is innovative for the following reasons:

- **New approach:** We propose a unique methodology that has been widely successful at reducing racial disparities in other fields. To our knowledge **values affirmation** has not been extensively evaluated as a health disparities intervention.
- **Sound theoretical concept –** The theoretical model (Figure 1) for which this proposal is based is supported by patient engagement theory. Our pilot study demonstrated that a single values-affirmation exercise improved subsequent patient-provider interaction and adherence, further supporting the validity of our theoretical approach.
- **Pragmatic:** Compared to existing interventions to improve adherence, values affirmation is significantly less time and resource intensive, enhancing the potential for the intervention to be embedded in primary care.
- **Evaluate for dissemination:** Using the RE-AIM (reach, effectiveness, adoption, implementation, maintenance) framework, we will formally evaluate the intervention for more widespread dissemination. Therefore, our approach will facilitate moving the intervention from a clinical trial to subsequent dissemination and implementation into clinical care.
- **Widely applicable:** Stereotype threat is not specific to hypertension outcomes or African Americans. Health care disparities have been demonstrated across numerous disease states and minority groups. Therefore, a simple intervention targeting a common mechanism has the potential to significantly reduce a wide range of health disparities.

### III. Preliminary Studies/Progress Report:

See section 1.6 for description of pilot studies.

### IV. Research Methods

**Overall strategy.** We will conduct a randomized controlled trial in African American and white patients with uncontrolled hypertension, comparing a values affirmation intervention to a control exercise in three healthcare systems. The primary outcome will be change in medication adherence with secondary outcomes of change in blood pressure, time under blood pressure control and treatment intensification. We will explore the mechanistic effects of the intervention and assess the suitability of the intervention for more widespread dissemination.

- A. Outcome Measure(s):** The primary outcome measure is medication adherence comparing adherence before and after the intervention. The secondary outcome measures are systolic blood pressure (comparing blood pressure at the index visit to blood pressure at 6-month follow-up), time under blood pressure control and treatment intensification.

**Primary Outcome: Medication adherence.** We plan to measure medication adherence in three ways. First, we will assess adherence using electronic pharmacy records as in our pilot study. Computerized pharmacy records have been used in a wide array of studies to assess medication adherence and correlate with other adherence measures such as electronic adherence monitors, self-report, and pill counts, and with treatment outcomes such as BP control. The measure of interest for the proposed study will be a summary measure of adherence which assesses the proportion of days covered (PDC) over the period of observation for which a patient obtains antihypertensive medications. Adherence will be calculated for each antihypertensive drug in the regimen and combined across drugs into a summary measure of adherence for the entire drug regimen using the method developed by [name] et al. We will calculate prior adherence using data from 12 months prior to the index visit to calculate change in adherence compared with the six months after the index visit. The investigator team has used this method to measure adherence in prior studies.

Second, because some patients will have only one refill opportunity (90-day supplies) over the 6-month follow-up period, we will also collect self-reported adherence at baseline, 3 and 6-months using the validated Voils instrument. The measure has three questions that address the *extent* of non-adherence over the previous 7 days.

Finally, we will validate the pharmacy and self-reported measures of adherence as assessed by pill counts. If  $x$  is the number of pills in the bottle,  $y$  is the number of pills that would have been in the bottle had all pills been taken since the bottle was filled, and  $z$  is the number of pills that should have been taken since the last fill, adherence is calculated as  $1 - [(x-y)/z]$ .

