### C. Study Design and Research Methods

[figure not shown]

**Overview:** The study design was developed in consultation with providers at the study sites to ensure feasibility of implementation in routine clinical practice. All primary care providers (PCP) at the participating clinics will be invited to complete a baseline survey regarding past disparities training and racial attitudes; patient participation will be independent of whether their PCP

participates. We will enroll self-identified African American and white patients with uncontrolled hypertension who are eligible and consent for the study. Our primary outcome is medication adherence that will be measured in three ways: 1) pharmacy fills, 2) self-report, and 3) pill counts. At the index visit, before they see their PCP, participants will have their blood pressure recorded and will complete a survey which includes a validated self-report measure of adherence (see Table 1 for survey contents). We will also query the EHR for baseline adherence based on prior 12-months pharmacy fills. Participants will be randomized to the values affirmation or control intervention tasks and they will complete the assigned task before seeing their PCP as scheduled. Following the visit, patients will complete a brief survey. Participants will return at 3-months and 6-months for in-person follow-up visits that will include assessment of adherence, blood pressure measurement and completion of surveys. Participants will be asked to bring all antihypertensive medications to each follow-up visit, and fill date and number of pills in the bottle will be recorded. Adherence will be calculated for each antihypertensive drug in the regimen and combined across drugs into a summary measure of adherence for the entire drug regimen. Secondary outcomes include blood pressure, time under blood pressure control, and appropriate treatment intensification. Throughout the study, we will evaluate the intervention for widespread dissemination based on the RE-AIM framework.

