**Evaluate for dissemination, RE-AIM.** The RE-AIM (Reach, Effectiveness, Adoption, Implementation, and Maintenance) framework will be used to evaluate the values affirmation intervention in order to enhance the quality, speed, and public health impact of translating the intervention into widespread clinical practice ([www.re-aim.org](http://www.re-aim.org)). [name], an ACCORDS investigator (primary research site) developed the RE-AIM model as an evaluation framework to expand assessment of interventions beyond efficacy to multiple criteria that may better identify the translatability and public health impact of interventions and that balances the emphasis on internal and external validity. We will apply RE-AIM by the examining the following:

**Reach** - the participation rate and representativeness of individuals who participate in the project. The participation rate is the proportion of patients who are approached who agree to participate in the study. The demographic and clinical factors of those who participate and those who do not will be compared to the same factors of the larger

population of patients with hypertension. Finally, we are deploying the intervention within three large health systems with varied demographic characteristics to increase the external validity.

**Effectiveness** – the impact of an intervention on outcomes. Since adherence is the target of the intervention, it will be the primary measure of effectiveness. Adherence will be measured at baseline and at 3- and 6-months to assess the impact and sustainability of the intervention at improving adherence. We will compare the effectiveness of the intervention to a control exercise in both African American and white patients to determine if the effect is dependent upon race. As discussed in the patient and providers' measures sections, we will also examine potential moderators of the intervention to understand whether the intervention is similarly effective across all groups. We will also compare the effectiveness according to baseline adherence and baseline blood pressure control.

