The primary outcome variable (adherence measured by pharmacy refills) is continuous; in the event that normality assumptions are not met we will use transformations to normalize distributions. For the primary comparisons, we will employ intent-to-treat analyses, although we expect few or none of the randomized patients to not complete an exercise. We will examine overall values affirmation effectiveness between the racial groups. We will next create models with adherence as the dependent variable including the potential moderator variable (prior experience of discrimination) then including the potential mediator variables (patient activation, attitude, social norms, perceived behavioral control, and anticipated emotion). Finally, we will explore whether the collected provider variables (racial bias, past cultural competency training, self-efficacy and racial mix of clinical site) moderate the relationships. We will also include patient gender and provider race as a possible moderating variables. We will use general (or generalized, for dichotomous outcomes) linear mixed models, examining alternative structures for the variance-covariance matrix for the level 1 model by comparing goodness of fit for the different models as well as model fitting diagnostics to assess for influential points, outliers, overdispersion and heteroscedasticity. We will employ methods that utilize all available data, assuming ignorable missingness.

In secondary analysis using the self-reported adherence measures, we will dichotomize the groups into non-adherent (score  $\geq 2$  on any "extent" item) and adherent. We will also compare the pill count measure of adherence to the pharmacy fill estimates of adherence for validation. For blood pressure, the secondary outcome, we will compare the index and follow-up visits using mixed effects repeated measures models with a patient random effect. All hypothesis tests will be two-sided with  $\alpha=.05$ . Statistical analysis will use SAS 9.4.

**Statistical Model for Primary Outcomes.** The structure of the data is hierarchical (patients nested within providers) and longitudinal (repeated measures on patients over time). Baseline (time 0) is defined as the adherence rate for the 12-months prior to the index visit.

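### Change in refill adherence sets 12 months before the visit against 6 months after it: the arm comparison is safe, but within-arm change, the control slope and the race slope among controls may not be

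*Protocol*

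**What the plan says.** The protocol fixes the pre-visit refill window at 12 months in three places.

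- Section IV.A (Primary Outcome: Medication adherence) derives "prior adherence using data from 12 months prior to the index visit to calculate change in adherence compared with the six months" of follow-up.
- Section IV.C (Overview): "We will also query the EHR for baseline adherence based on prior 12-months pharmacy fills".
- Section IV.F (Statistical Model for Primary Outcomes): "Baseline (time 0) is defined as the adherence rate for the 12-months prior to the index visit". Post-baseline values are then coded by days since baseline, and arm, race and arm-by-race terms act on both intercept and slope.

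The pilot, in the first of the two sections numbered 1.7, was built differently: "pharmacy records were used to compare adherence in the six-month period before the index visit with the six-months after the index visit". Its results are laid out as before/after means within each arm (74% to 83%, and 83% to 81%). Section IV.A introduces the trial measure thus: "First, we will assess adherence using electronic pharmacy records as in our pilot study".

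Section IV.A also notes that some patients on 90-day supplies will have a single refill opportunity in the six months of follow-up. Under RE-AIM, Effectiveness, Section IV.C says: "Adherence will be measured at baseline and at 3- and 6-months to assess the impact and sustainability of the intervention at improving adherence".

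**The concern.** PDC is a ratio over a window. Unless supply already in hand on the first day is credited, the result depends on how long the window is. If only fills inside the window count, the uncovered days before the first fill are a larger share of a short window, so the shorter window reads lower. If counting starts at the first fill, the shorter window reads higher. Both effects grow with supply length.

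A 12-month value set against a 6-month value can therefore show change where adherence has not changed. The quantities exposed are those not formed by comparing randomised arms: change within an arm, the control growth rate, and the race difference in slope among controls (beta12 in Section IV.F). Race is not randomised, so the artefact leaves beta12 only if supply patterns are alike in the two groups. Readers are also likely to set the trial's within-arm changes beside the pilot's, which used equal windows.

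**Working it through.** **The plan's own figure.** Inputs from Section IV.F: effect 0.26 SD, two-sided alpha 0.05, power 80%, 240 per cell, attrition 15%. n = 2(1.960 + 0.842)²/0.26² = 233 per cell, against 240 planned (power 81.3%). 960/0.85 = 1,130. The stated 4.7 points implies an SD of 4.7/0.26 = 18.1. These figures reproduce and do not depend on the baseline window. The 4.7 points is a difference between cells.

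**Size of the artefact when only in-window fills count.** Assume stationary refilling, supply length L and true coverage a. On the first day of a window a patient is covered with probability a, with on average L/2 days left. Ignoring that supply loses aL/2 days, or aL/(2W) of a window of W days. Spurious change = -(aL/2)(1/180 - 1/365). Take a = 0.812 (assumed, close to the pilot's level):

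- L = 90 (a supply length named in Section IV.A): 0.812 × 45 = 36.5 days; 36.5/365 = 10.0 points; 36.5/180 = 20.3 points; change = -10.3.
- L = 30 (assumed): 0.812 × 15 = 12.2 days; 3.3 and 6.8 points; change = -3.4.

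**Simulation with no true change at the visit** (6 months after minus 12 months before, in points). Run A had mean PDC about 81% with 180-day half-year windows. Run B had mean PDC about 73% to 80% with 182-day windows.

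| PDC rule | Supply | Run A | Run B | Equal windows, run B |
|---|---|---|---|---|
| In-window fills only | 30 days | -3.5 | -2.9 to -3.2 | -0.2 to 0.1 |
| | 90 days | -10.3 | -9.5 to -9.9 | -0.9 to 0.4 |
| From first fill | 30 days | +1.3 | +1.4 to +2.2 | 0.0 to 0.3 |
| | 90 days | +6.2 | +6.4 to +8.1 | 0.1 |
| Carry-in credited | 30 or 90 days | 0 | -0.5 to +0.2 | -0.6 to 0.3 |

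A third run gave about -11 and +7 for 90-day supplies, and -3.5 and +1 for 30-day supplies. Equal windows remove the shift under every rule, apart from simulation noise.

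**Arm contrast.** The baseline window ends at the index visit, so its expected value is the same in both arms of a race stratum whatever its length. If window length adds d to the change in each arm, (I + d) - (C + d) = I - C. With a simulated benefit, the arm difference in change for 12/6 against 6/6 windows was 2.75 against 2.78 (carry-in credited), 2.85 against 3.06 (in-window fills) and 3.59 against 3.49 (first fill), with standard errors of 0.20 to 0.28. The same holds for the difference of these contrasts between races.

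**Race slope among controls.** Under the in-window rule, each 10-percentage-point difference between races in the share on 90-day supplies moves beta12, expressed as six-month change, by 0.10 × (10.3 - 3.4) = 0.7 points. The real shares are not in the protocol.

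**Change or covariate in the arm comparison.** With one baseline and one follow-up value, complete data and arm-specific intercepts, the slope contrast is a contrast of mean changes. Let k = SD(12-month pre)/SD(6-month post) and r their correlation. Relative to the post-visit variance, a change has variance 1 + k² - 2rk and a covariate-adjusted value 1 - r². From run B at the lower adherence level:

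- Mixed supplies, carry-in credited: k = 17.3/19.8 = 0.874, r = 0.60; 0.72 against 0.64.
- 90-day, in-window fills: k = 17.8/22.0 = 0.809, r = 0.33; 1.12 against 0.89.
- 90-day, first fill: k = 12.3/11.9 = 1.034, r = 0.09; 1.88 against 0.99.

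**A 3-month value.** A 180-day baseline does not repair a 90-day follow-up window. With 90-day supplies, 90 days after minus 180 days before gave about -21 points (in-window fills) or +9 (first fill), and about 0 with carry-in credited.

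**The case against.** The strongest reply is that no tested hypothesis is harmed. H1 compares arms and H3 compares that effect between races; both rest on randomised contrasts (beta11, beta13), and randomisation is stratified by race at each site. The analysis plan contains no within-arm before/after test, and beta12 belongs to no stated hypothesis. This stands in full. A reader might infer that unequal windows bias the primary result or the race interaction; the documents do not support that.

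Next, the size depends on a PDC rule that the protocol leaves to a cited method. Carry-in handling is ordinary material for an analysis plan, and Section IV.D says the data warehouses go back to 2004, so earlier fills can be obtained. This also stands. Window length by itself does nothing if carried-in supply is credited. Setting 10 points beside 4.7 would be misleading, since 4.7 is a between-cell difference from which the artefact cancels.

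Two further inferences fail. The reference to the pilot in Section IV.A reads most naturally as using pharmacy records as the pilot did, so the different window is an unexplained departure rather than a contradiction. And a 3-month refill value is only inferred from RE-AIM: Table 3 gives the 3- and 6-month schedule to self-report and pill counts, and lists refill adherence as ongoing.

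Finally, a 12-month baseline predicts the post-visit value a little better (correlation 0.60 against 0.53 with mixed supplies and carry-in credited). That supports it as a covariate, but not as the value from which change is formed.

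**Conclusion.** The point holds in a limited form. The protocol forms change in refill adherence from windows of unequal length, where its pilot used equal ones. The randomised arm contrast and the arm-by-race contrast are unbiased, and the sample size is unaffected. The within-arm change, the control growth rate and beta12 can be displaced by about -3 to -11 or +1 to +7 points (8.1 in the low-adherence 90-day scenario of run B) if carried-in supply is not fully credited, and by about nothing if it is. These figures assume stationary refilling, 30- or 90-day supplies and mean PDC of about 73% to 81%. The protocol gives neither the rule nor the supply mix, so neither the sign nor the size is known for this trial. What justifies a change is that the exposed quantities are likely to be reported or read off the model, and that the remedy is cheap.

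**What to change.** 1. For any reported before/after change in refill adherence, compute pre-index PDC over the 180 days before the visit, with the same algorithm and carry-in rule as the 180 days after it.
2. If a 3-month refill value is reported, compare it only with windows of equal length (90 days), or credit carried-in supply throughout.
3. In the arm comparison, model the post-visit PDC with the 12-month PDC as a baseline covariate, instead of entering the latter as the time-0 outcome.
4. State that beta12 and the control growth rate will not be interpreted from unequal windows.

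Cost: one more derived variable from the pharmacy extract already planned, and a small edit to the primary model in Section IV.F, so this is slightly more than a change of wording. The 180-day baseline is noisier than the 12-month one, which is the reason to keep the latter as the covariate.
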